### Study design

This RCT is an investigator-initiated, randomized, controlled, parallel group, and non-inferiority trial comparing laparoscopic D2 lymphadenectomy for locally AGC patients with open conventional surgery.

Before enrollment of first patient, this study was approved from the institutional review boards (AJIRB-MED-MDB-11-223) of Ajou university hospital, Soonchunhyang university hospital, Keimyung university hospital, Chonnam national university hwasun hospital, Incheon St. Mary’s hospital, Yeoeuido St. Mary’s hospital, Dong-A university hospital, Seoul national university hospital, Seoul national university bundang hospital, Yonsei university severance hospital, Yonsei university gangnam severance hospital, Ewha womans university hospital and National cancer center. All investigators progress this study in accordance with the Declaration of Helsinki [9]. An independent institutional review board of all institutions at which the participating surgeons are affiliated has approved this study. Written informed consent will be obtained from all patients before they are recruited. This RCT will be monitored by an independent data and safety monitoring committee (DSMC) organized by the Clinical Trial Center of Ajou University Hospital.

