### Sample size calculation

The primary endpoint of this RCT is 3-year relapse-free survival of patients diagnosed with locally AGC. In an RCT conducted by Sakuramoto et al. [9], the 3-year relapse-free survival of gastric cancer patients who received TS-1 adjuvant chemotherapy and were diagnosed with stage II or III cancer on pathology from curative gastrectomy with D2 lymph node resection was 72% (hazard rate = 0.11). Therefore, the hazard rate of patients who underwent open conventional surgery in the control condition was 0.11 in the 3 year. In addition, the margin of non-inferiority assumed a hazard ratio (HR; hazard rate of group A/hazard rate of group B) of 1.43 according to the study design in the Sakuramoto et al., in which the HR of the surgery-only group was compared with that of the adjuvant group. The null hypothesis was assigned as HR ≥ HR_0_, and the alternative hypothesis as HR < HR_0_. Type I error was set at 0.25 (one-sided) with 90% power, and the sample size was calculated using the log-rank test for non-inferiority (PASS 12. NCSS, LLC. Kaysville, Utah, USA. www.ncss.com.).

As a result, a total of 1,050 patients (525 patients per group) with 330 target event as recurrence are required when we consider a 10% dropout rate.

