### Patient groups for statistical analysis

The efficacy for the primary and secondary outcomes will be evaluated in different groups of patients according to the surgical results. Except for the patients who are not undergoing surgery or have unresectable tumors, all patients will be included in the intention-to-treat (IIT) group. The postoperative recovery, morbidity and mortality, quality of life, and overall survival will be evaluated for the patients in IIT group. The 3-year relapse-free survival will be analyzed for patients in the full analysis set (FAS) group. ITT group patients who cannot undergo curative resection and have synchronous tumors or distant metastases un-defined at the screening step, will be additionally excluded from the FAS group. If patients did not comply with protocol because of various reasons like as conversion of surgical type, total resection and follow up loss, then they will be excluded from the per-protocol (PP) group. When the difference between the FAS and PP groups exceeds 10% of the total recruitment number, statistical analysis with the PP group patients will be performed. This RCT is schematically described in Figure 1. For safety analysis, patients in FAS group are examined with their actual treated surgery.

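### The per-protocol analysis of relapse-free survival depends on a mixed 10% exclusion count and drops patients lost to follow-up; it should always be reported, with those patients censored

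*Protocol article*

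**What the plan says.** The Protocol article, Study design, states: "This RCT is an investigator-initiated, randomized, controlled, parallel group, and non-inferiority trial". The section Patient groups for statistical analysis then fixes three things.

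- **Primary set:** "The 3-year relapse-free survival will be analyzed for patients in the full analysis set (FAS) group".
- **PP exclusions:** "If patients did not comply with protocol because of various reasons like as conversion of surgical type, total resection and follow up loss", they leave the PP set.
- **When PP is analysed:** "When the difference between the FAS and PP groups exceeds 10% of the total recruitment number, statistical analysis with the PP group" patients is performed.

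No other part of the article provides for a PP analysis of RFS that does not depend on this count. The statistical methods paragraph after Figure 1 names Kaplan-Meier curves and log-rank tests for RFS. Under Sample size calculation, "a total of 1,050 patients (525 patients per group) with 330 target event as recurrence are required when we consider a 10% dropout rate", and "the margin of non-inferiority assumed a hazard ratio (HR; hazard rate of group A/hazard rate of group B) of 1.43".

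**The concern.** In a non-inferiority trial, departures from the allocated operation can make the arms look more alike, and likeness is what the trial sets out to show. The PP analysis is the article's only stated look at this, and the rule makes it conditional on how many patients are excluded. Three features of the rule matter.

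- **The count is pooled over both arms.** Conversion, as defined under Laparoscopic procedure, occurs only in the laparoscopic arm. A limit of 10% of all patients is therefore 20% of the one arm where conversion can happen.
- **The count mixes different things.** Loss to follow-up is not a treatment deviation, yet it counts the same as a conversion. Many conversions with complete follow-up can leave PP unrun, while few conversions with poor follow-up can trigger it.
- **The PP set itself is flawed when it is run.** Excluding a patient for loss to follow-up discards event-free time that a survival analysis is built to use.

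At stake is whether a conclusion of non-inferiority rests on the FAS alone, with no view of how sensitive it is to the operation actually performed.

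**Working it through.** **1. The plan's event target.** Inputs from Sample size calculation: margin HR 1.43, 90% power, 330 events. The article prints "Type I error was set at 0.25 (one-sided) with 90% power".

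Schoenfeld: D = 4(z_alpha + z_beta)^2 / (ln 1.43)^2, with ln 1.43 = 0.3577.

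- One-sided 0.025: 4(1.960 + 1.282)^2 / 0.3577^2 = 329 events, against 330 stated.
- One-sided 0.25: 4(0.674 + 1.282)^2 / 0.3577^2 = 120 events.

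The target is reproduced with 0.025 and not with the printed value, so 0.025 is assumed below. The printed value is a separate matter.

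**2. The trigger.** 0.10 x 1,050 = 105. The rule requires the difference to exceed this, so 105 or fewer exclusions give no PP analysis. With 525 per arm, 105/525 = 20%.

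**3. How many conversions can pass.** No PP analysis is triggered while conversions + total resections + losses <= 105. With total resections set to zero:

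| Losses to follow-up | Most conversions without PP | Share of laparoscopic arm |
|---|---|---|
| 0 | 105 | 20% |
| 53 | 52 | 9.9% |
| 79 | 26 | 5.0% |
| 105 | 0 | 0% |

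The planned 10% dropout is itself 105 patients. If all of it were loss to follow-up within the FAS, one further exclusion of any kind would trigger PP.

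**4. Size of possible dilution.** Assumptions: the HR for completed laparoscopy versus open is 1.43; a fraction f of the laparoscopic arm converts and carries the open-arm hazard; 330 events; one-sided 0.025. Then

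P(false non-inferiority) = Phi( (ln 1.43 - ln HR_FAS) x sqrt(330)/2 - 1.960 ), with sqrt(330)/2 = 9.083.

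At f = 0.20:

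- *Log-HR dilution:* HR_FAS = 1.43^0.8 = 1.331; Phi(0.20 x 0.3577 x 9.083 - 1.960) = Phi(-1.310) = 9.5%.
- *Survival mixture at 3 years, open hazard 0.11 per year:* open survival exp(-0.33) = 0.7189; completed laparoscopy exp(-0.33 x 1.43) = 0.6238; mixture 0.8 x 0.6238 + 0.2 x 0.7189 = 0.6428; HR_FAS = -ln(0.6428)/0.33 = 1.339; Phi(-1.363) = 8.6%.
- *Average of hazards:* 0.8 x 1.43 + 0.2 = 1.344, giving 8.1%. This is the HR at time zero. It falls as higher-hazard patients leave the risk set, so 8.1% is a low edge.
- *Simulation* (4,000 trials, three-year accrual assumed, Cox model at the 330th event): 8.9%, against 2.4% with no conversions.

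At 52 conversions the approximations give 4.6-5.1% (simulation 5.1%); at 26 they give 3.4-3.6% (simulation 3.6%).

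**5. Loss to follow-up.** A patient lost before relapse contributes event-free time up to last contact. Censoring keeps that time. Exclusion removes it, while patients whose relapse was recorded remain. The estimated hazard rises in any arm where this is done. With equal loss in the two arms the HR moves little; with unequal loss it can move, towards the arm that lost fewer patients. The article says under Study protocol that surgeons and patients cannot be blinded, so equal loss cannot be taken for granted.

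**The case against.** **The bound is a stress case.** Reaching 105 conversions requires no losses and no total resections in either arm. The article gives no conversion rate, and surgeons are screened by video review and by at least 50 earlier laparoscopic gastrectomies. This stands: a reader might infer that about 105 diluting deviations are to be expected, and the documents do not support that. The range is 0 to 105. Nor can the pooled exclusions be assumed to fall mostly in one arm, since of the named reasons only conversion is specific to laparoscopy.

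**The bias need not favour non-inferiority.** The article defines conversion as an added incision, for bleeding or another reason, before laparoscopic lymphadenectomy is complete. Such patients have had part of the laparoscopic procedure and may be the harder cases. Keeping them in the laparoscopic arm could then count against laparoscopy, and a PP set without them could be the more lenient one. This stands too. It argues for seeing the PP result both ways, not for making it conditional.

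**Counting losses makes PP more likely to run.** True, but then the trigger responds to follow-up quality and not to the treatment received.

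**The primary analysis is untouched, and fuller documents may add sensitivity analyses.** The FAS analysis of RFS can censor lost patients as it is. Figure 1, whose legend mentions PP, is not visible, and the article does not say that PP is run only above the threshold. Still, this is a stated rule, and a condition for performing an analysis has little purpose if the analysis is performed anyway.

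**Conclusion.** The point holds as a defect in the robustness check, not in the primary analysis. The rule ties the PP analysis of a non-inferiority endpoint to a count that does not measure treatment deviation, and it builds the PP set by discarding patients who could be censored.

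At the upper bound of 105 conversions, an HR of 1.43 would be diluted to about 1.33-1.34 and false non-inferiority would be about 8.6-9.5% in place of 2.5%. This rests on four assumptions: all exclusions are conversions, converted patients carry the open-arm hazard, there are 330 events, and alpha is one-sided 0.025. With fewer conversions the inflation shrinks. If converted patients are harder cases, the direction may reverse. The effect of dropping lost patients on the HR depends on a difference in loss between arms, for which the article gives no figure.

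A reader might also infer that non-inferiority must be shown in both sets. The documents do not commit to that. A single pre-specified primary set with PP reported as supportive is an accepted choice, and requiring both is a trade-off against power.

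**What to change.** In Patient groups for statistical analysis:

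1. Delete the 10% condition. State that the PP analysis of RFS is always reported beside the FAS, with the confidence interval for the HR set against the 1.43 margin.
2. Remove loss to follow-up from the PP exclusions. Censor those patients at their last disease evaluation in both sets.
3. Because conversion occurs in one arm only, show the PP result with and without converted cases.
4. State that any disagreement between PP and FAS will be discussed before non-inferiority is concluded.

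The cost is one or two further runs of the same analysis. Conversions are already to be recorded in the eCRF, and the sample size does not change.

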#### Laparoscopic procedure

Preoperative insertion of nasogastric tube is performed depending on each surgeon’s discretion. Prophylactic antibiotics are injected within 30 minutes before skin incision. The location and number of trocars are not limited. Surgeons will examine the abdominal cavity to determine whether there is no metastatic lesion or if the gastric cancer is resectable. If the patient has unexpected metastatic lesions or the surgeon decides that curative resection of tumor is impossible, the operation is stopped and the patient is excluded from this RCT. Washing cytology could be performed by inserting 50 cc of saline solution into the pelvic cavity. Then, the surgeon begins the D2 lymphadenectomy including total omentectomy. The guideline for D2 lymphadenectomy in locally AGC patients is shown in Table 1. If surgeons make an additional abdominal incision to control bleeding or for any other reason before finishing the laparoscopic D2 lymphadenectomy, they will record this situation as “conversion to open” in the eCRF system. After lymphadenectomy, the reconstruction methods are not limited in this RCT. The surgeon can perform one of the Billroth-I, Billroth-II, or Roux-en Y methods for reconstruction, which can be carried out by minilaparotomy. Hand-sewing or using staplers for anastomosis are not limited, and drain insertion is left to the discretion of each surgeon.

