### Safety assessment for early morbidity

When the safety analysis group reaches 484 patients, analysis will be performed to evaluate the safety of laparoscopic subtotal gastrectomy with D2 lymphadenectomy. Considering the reports of Sano et al. [11] and Deguili et al. [12], the complication rate of standard gastrectomy with D2 lymph node dissection was estimated at 20.9% and the margin of non-inferiority for the complication rate was assumed to be 12%. With a type I error of 0.025 (one-sided) and 90% power, 242 patients in each safety analysis group are required. When a total of 484 patients are enrolled in the safety analysis groups, the steering committee will decide whether this trial would be continued according to the results of this safety analysis.

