The safety of laparoscopic D2 lymphadenectomy should be emphasized, because this study is the first multicenter RCT to evaluate its efficacy. In our RCT, morbidities related to surgeries will be investigated separately during early and late postoperative periods after surgery. Since most late complications such as reflux and intestinal obstruction are mainly related to reconstruction methods regardless of the type of laparoscopic or open laparotomy, we eventually focused on early postoperative morbidity to evaluate safety. When the number of patients recruited in this RCT reaches 484, the data related to early postoperative morbidities will be analyzed to determine whether laparoscopic surgery for D2 lymphadenectomy is less safe compared with open surgery. The number of patients required for this safety analysis was calculated according to previous RCTs, which reported that the complication rate of D2 lymphadenectomy was 20.9% in an RCT performed by Japanese surgeons, and the limitation of non-inferiority for complications of D2 lymphadenectomy compared with D1 was 12.0% in another Italian RCT [11,25]. This protocol includes a plan to stop recruitment and discontinue this RCT if the results of the safety analysis show significant inferiority in the safety of laparoscopic groups relative to the conventional group.

In conclusion, the KLASS-02 RCT was designed to show the efficacy of laparoscopic D2 lymphadenectomy in AGC patients compared with the open procedure. We attempted to highlight the principle of surgical clinical trials, and the internal validity of surgeons participating in this RCT was considered. Finally, we hope to suggest our RCT to other researchers who wish to conduct a well-designed, organized surgical clinical trial.

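### The 484-patient safety decision is grouped by surgery received in the FAS, which most naturally counts converted laparoscopic cases as open and can bias it toward non-inferiority

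*Protocol article*

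**What the plan says.** All places are in the protocol article.

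- **Patient groups for statistical analysis** fixes the set and grouping for safety: "For safety analysis, patients in FAS group are examined with their actual treated surgery". The same section says: "The postoperative recovery, morbidity and mortality, quality of life, and overall survival will be evaluated for the patients in IIT group" (IIT is the article's spelling of ITT). The ITT group leaves out patients who were not operated on or whose tumour was unresectable. The FAS further removes those without curative resection and those with synchronous tumours or metastases not known at screening. Conversion is a reason for exclusion only from the per-protocol group, so converted patients stay in the FAS.
- **Laparoscopic procedure** has surgeons record a conversion to open if they "make an additional abdominal incision to control bleeding or for any other reason before finishing the laparoscopic D2 lymphadenectomy".
- **Safety assessment for early morbidity** sets the timing: "When the safety analysis group reaches 484 patients, analysis will be performed to evaluate the safety of laparoscopic subtotal gastrectomy with D2 lymphadenectomy". It assumes a complication rate of 20.9% and a margin of 12 percentage points, and gives the size: "With a type I error of 0.025 (one-sided) and 90% power, 242 patients in each safety analysis group are required". It then says that "the steering committee will decide whether this trial would be continued according to the results of this safety analysis".
- **Discussion** describes a plan to "stop recruitment and discontinue this RCT if the results of the safety analysis show significant inferiority" of the laparoscopic group.

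**The concern.** Conversion happens after randomisation and during the operation. The article describes it only from laparoscopic to open, and names bleeding as one reason. Under grouping by surgery received, the natural reading is that a patient allocated to laparoscopy and then opened is counted with the open group. If such patients have more complications than other laparoscopic patients, the move lowers the laparoscopic rate and raises the open rate together. The comparison is then no longer the randomised one, and it errs toward continuing with the experimental procedure.

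Grouping by treatment received is conventional for descriptive safety tables. Here, however, the analysis carries a non-inferiority test and a continue-or-stop decision, and the event that reclassifies patients may itself be a consequence of the laparoscopic approach.

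Two further points touch the same decision. The article does not say whether the ITT statement on morbidity or the FAS statement on safety governs the 484-patient look. And the FAS omits operated patients without curative resection, although they were exposed to the surgery.

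**Working it through.** **Inputs from the article:** open complication rate 20.9%; margin 12 points; one-sided alpha 0.025; power 90%; 242 per group.

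**Assumed inputs (not in the article):** proportion *c* of laparoscopic patients converted, 2% to 10%; complication rate *p_c* in converted patients, 40% to 60%, or equal to the laparoscopic average.

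**1. The article's own figure.** Unpooled normal approximation, equal true rates:

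n = (1.960 + 1.282)² × 2 × 0.209 × 0.791 / 0.12² ≈ 10.51 × 0.3306 / 0.0144 ≈ 241.3, so 242 per group. The stated size is reproduced. Power at 242 per group is 90.1%.

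**2. Comparison by allocated arm at the margin.** With laparoscopic 32.9% and open 20.9%, the standard error is √[(0.329 × 0.671 + 0.209 × 0.791)/242] = 0.0399. The chance of concluding non-inferiority is Φ((0.12 − 0.12)/0.0399 − 1.96) = 2.5%, as designed.

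**3. Comparison by surgery received.** Let p_L and p_O be the rates by allocation. After converted cases move to open:

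- laparoscopic rate = (p_L − c·p_c)/(1 − c), with 242(1 − c) patients
- open rate = (p_O + c·p_c)/(1 + c), with 242(1 + c) patients
- chance of concluding non-inferiority = Φ((0.12 − difference)/SE − 1.96)

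Worked case, c = 5%, p_c = 50%, true excess 12 points:

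- laparoscopic (0.329 − 0.025)/0.95 = 32.0% of 229.9 patients
- open (0.209 + 0.025)/1.05 = 22.3% of 254.1 patients
- apparent difference 9.7 points; SE = √(0.320 × 0.680/229.9 + 0.223 × 0.777/254.1) = 0.0403
- Φ(0.0229/0.0403 − 1.96) = Φ(−1.39) = 8.2%

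| Converted | Complications in converted | Apparent difference, true difference 0 | Apparent difference, true excess 12 | Chance of non-inferiority at true excess 12 |
|---|---|---|---|---|
| By allocation | – | 0 | 12.0 | 2.5% |
| 2% | 40% | −0.8 | 11.5 | 3.4% |
| 5% | 50% | −2.9 | 9.7 | 8.2% |
| 10% | 50% | −5.9 | 7.5 | 19.9% |
| 10% | 60% | −7.9 | 5.4 | 36.4% |

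Differences are laparoscopic minus open, in percentage points.

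**4. The favourable case.** If converted patients carry only the laparoscopic average risk, the laparoscopic rate does not move and the open rate changes by c(p_L − p_O)/(1 + c). At equal rates this is 0. At a 12-point excess it is 0.02 × 12/1.02 = 0.24 points for 2% converted and 0.10 × 12/1.10 = 1.09 points for 10%. The chance of wrongly concluding non-inferiority is then 2.9% to 4.5%.

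The effect of dropping operated patients without curative resection cannot be sized: the article gives neither their number nor their complication rate.

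**The case against.** The strongest objection is that the premise is inferred. No sentence says which group a converted case joins, and surgery received could mean the procedure begun rather than the one completed. This stands as a limit on certainty. It does not remove the point, because the recorded label is conversion to open and an unsettled rule could be settled after the data are seen.

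Nor does the article say that conversions usually follow complications. Bleeding is named, but so is any other reason, and operative blood loss is recorded apart from the listed morbidity events. The conversion inputs are unsourced, and with rare conversion the effect is small. Even at 5% and 50%, about 92% of trials at the margin would still fail to show non-inferiority. All of this stands.

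A reader might infer three stronger things that the article does not support:

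- *That the ITT and FAS sentences flatly contradict each other.* They can be read as two analyses: morbidity as a secondary outcome, and a separate safety analysis. What is missing is a statement of which one drives the decision.
- *That there are two conflicting stopping rules.* If the Discussion meant a test against zero, it would be met from an observed excess of about 7.7 points, while non-inferiority fails from about 4.5. But the Discussion does not define its test and may be paraphrasing the sized criterion loosely. The wording needs aligning; a conflict is not shown.
- *That independent oversight is bypassed because the steering committee decides.* The article names an independent monitoring committee and nothing excludes its advice. Detailed roles are commonly left to the full protocol or a charter.

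Finally, widening the set to everyone in whom surgery was started would bring in operations stopped at exploration. If these have few complications in either arm, they dilute the difference and also favour non-inferiority. The fix takes this into account.

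**Conclusion.** The concern holds in a qualified form. The sample size is right; the set and grouping are poorly fixed for an analysis that decides whether the trial continues. The direction of bias is toward laparoscopic non-inferiority, provided that converted cases count as open and have more complications than the rest. Both conditions are plausible and neither is stated. At a true 12-point excess, the error rises from the designed 2.5% to about 3.4%, 8% or 20% in the three main scenarios. If conversion is rare or carries average risk, the effect is small. The article therefore does not show that laparoscopy will look safer than it is, only that the stated rule allows it. That is enough to change the rule before the 484-patient analysis is run, since the randomised comparison avoids this reclassification bias at no cost in size.

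**What to change.** - In *Patient groups for statistical analysis* and *Safety assessment for early morbidity*, state that the 484-patient early-morbidity comparison uses the ITT group as the article defines it, by allocated arm, with converted cases kept in the laparoscopic arm.
- Keep the FAS comparison by surgery received as supportive, and say explicitly how converted cases are classified in it.
- Report patients whose operation was stopped at exploration separately or in a sensitivity analysis.
- Align the Discussion wording with the 12-point, one-sided 0.025 non-inferiority criterion for which the analysis was sized.

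The size stays at 242 per group. Allocation and conversion are already captured in the eCRF system, so the cost is an amendment of wording and no new data.

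### Grouping the safety analysis by surgery actually received appears to move converted laparoscopies into the open group at the 484-patient continuation decision, and it conflicts with the intention-to-treat statement on morbidity

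*Protocol article*

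**What the plan says.** All references are to the protocol article.

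- **Patient groups for statistical analysis** sets the grouping rule for safety: "For safety analysis, patients in FAS group are examined with their actual treated surgery".
- **Laparoscopic procedure** defines conversion: "If surgeons make an additional abdominal incision to control bleeding or for any other reason before finishing the laparoscopic D2 lymphadenectomy", the case is entered in the eCRF as converted to open.
- **Patient groups for statistical analysis** lists conversion among the departures from protocol: for "various reasons like as conversion of surgical type, total resection and follow up loss, then they will be excluded from the per-protocol (PP) group". Nothing removes these patients from the full analysis set (FAS), so they are part of the safety comparison.
- **Safety assessment for early morbidity** attaches a decision to that comparison: "When a total of 484 patients are enrolled in the safety analysis groups, the steering committee will decide whether this trial would be continued". The **Discussion** adds the consequence: "This protocol includes a plan to stop recruitment and discontinue this RCT if the results of the safety analysis show significant inferiority".
- **Patient groups for statistical analysis** also says, a few sentences before the safety rule: "The postoperative recovery, morbidity and mortality, quality of life, and overall survival will be evaluated for the patients in IIT group".

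Complications are thus assigned to two populations: the intention-to-treat group, and the FAS by surgery received. No sentence says which arm a converted patient belongs to in the safety analysis.

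**The concern.** Grouping by treatment received is a common convention for safety sets and works when exposure is clean. Conversion is different. It happens after randomisation, it is a consequence of attempting laparoscopy, and only the laparoscopic arm can produce it. Bleeding is the article's own example of a reason. If converted patients are counted as open, some failed laparoscopies, with their complications, leave the laparoscopic group and join the comparator.

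The question at the 484-patient look is whether choosing laparoscopy is less safe than choosing open surgery, and the risk of conversion is part of that choice. If converted patients carry a high complication rate, the rule makes a false finding of non-inferior safety more likely and a finding of significant inferiority less likely. The look is a formal comparison of morbidity on which continuation depends.

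**Working it through.** **Inputs from the article** (Safety assessment for early morbidity): complication rate 20.9%, margin 12 points, one-sided type I error 0.025, power 90%, 242 per group.

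**Assumptions, not in the article:** *c*, the share of the laparoscopic arm that is converted, and *q*, the complication rate in converted patients.

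**Step 1: the plan's own figure.** With equal rates and unpooled variance,

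n = (1.960 + 1.282)² × 2 × 0.209 × 0.791 / 0.12² = 241.3, rounded up to 242 per group and 484 in total. The stated size reproduces; power at 242 is 90.1%.

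**Step 2: rates after regrouping.** Let pO = 0.209 and pL = 0.329, so that laparoscopy as randomised lies exactly at the margin. If converted patients count as open:

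- laparoscopic rate = (pL − cq)/(1 − c), on 242(1 − c) patients
- open rate = (pO + cq)/(1 + c), on 242(1 + c) patients

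With d the difference between these rates and SE its unpooled standard error:

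- P(pass non-inferiority) = Φ((0.12 − d)/SE − 1.96)
- P(show inferiority) = Φ(d/SE − 1.96)

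**Step 3: one case in full, c = 5% and q = 50%.**

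- Laparoscopic: (0.329 − 0.025)/0.95 = 0.3200
- Open: (0.209 + 0.025)/1.05 = 0.2229
- d = 0.0971; SE = √(0.3200 × 0.6800/229.9 + 0.2229 × 0.7771/254.1) = 0.0403
- P(pass) = Φ(0.0229/0.0403 − 1.96) = Φ(−1.39) = 8.2%
- P(inferior) = Φ(0.0971/0.0403 − 1.96) = Φ(0.45) = 67%

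**Step 4: range, with a true excess of 12 points throughout.**

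| c | q | Apparent excess (points) | False non-inferiority | Inferiority shown |
|---|---|---|---|---|
| as randomised | – | 12.0 | 2.5% | 85% |
| 2% | 32.9% | 11.8 | 2.9% | 84% |
| 2% | 50% | 11.1 | 4.2% | 79% |
| 5% | 20.9% | 12.6 | 1.7% | 88% |
| 5% | 32.9% | 11.4 | 3.5% | 81% |
| 5% | 50% | 9.7 | 8.2% | 67% |
| 8% | 50% | 8.4 | 14.4% | 54% |

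**Step 5: direction.** The shift in the difference is c(pL − q)/(1 − c) − c(q − pO)/(1 + c). It is zero at q = [pL(1 + c) + pO(1 − c)]/2. At c = 5% this is (0.34545 + 0.19855)/2 = 27.2%, close to the midpoint of the two arm rates. Above that value the regrouping favours laparoscopy; below it, the effect reverses.

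**The case against.** Four points can fairly be made against the concern.

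1. **The reclassification is inferred.** The article never says that a converted patient counts as open for safety. The grouping rule could be meant only for patients who never had their allocated approach, with a started laparoscopy remaining laparoscopic. This stands as a limit on certainty. But the article records these cases as conversions to open, calls them a change of surgical type, and nowhere keeps them under laparoscopy. A full protocol might settle it; the rule as printed points the other way.
2. **Morbidity is also to be evaluated by intention to treat.** That analysis would keep converted patients in their arm. However, continuation is tied specifically to the safety analysis ("the steering committee will decide whether this trial would be continued according to the results of this safety analysis"), and the grouping rule uses the same term. The intention-to-treat sentence shows a conflict; it does not settle which analysis governs.
3. **The direction is not fixed.** A reader might infer that the bias always favours laparoscopy, or that it vanishes only when converted patients fare no worse than others. Neither is correct: in the scenario above the shift is zero near q = 27% and reverses below it. Conversions may be for any reason, so low-risk ones are possible.
4. **The size may be small.** Surgeons are validated by video review and must have done at least 50 laparoscopic gastrectomies, which makes high conversion less likely without excluding it. At 2% conversion and average risk the error rate barely moves. The primary endpoint is relapse-free survival, an independent committee monitors the trial, and reasons for conversion are recorded. These limit the consequence but do not define the comparison.

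**Conclusion.** The point holds in a conditional form. On the plain reading, the safety rule places converted laparoscopies with the open group in the comparison that decides continuation, and it conflicts with the intention-to-treat statement on morbidity. A reader might infer that the article states this counting outright or that the decision is certain to be biased towards laparoscopy. The text supports neither.

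If converted patients do count as open, the effect is negligible to small at 2% conversion with average risk (2.9% against a nominal 2.5%). It is material at 5% to 8% conversion when half of the converted patients have a complication (8.2% to 14.4%, with the chance of showing inferiority falling from 85% to 67% and 54%). At 5% conversion it turns slightly conservative if converted patients have only the open rate (1.7%). All of these figures rest on assumed values of *c* and *q*, a true excess equal to the margin, and a normal approximation. The defect should be corrected because a continuation decision depends on it, but it does not undermine the trial's primary comparison.

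**What to change.** Replace the safety-grouping sentence with one stating that the 484-patient look and the final safety comparison are made by randomised arm, and that converted patients remain in the laparoscopic arm. In the same edit, reconcile this with the sentence that assigns morbidity to the intention-to-treat group, so that one population is named for the complication comparison and for the decision. Report the table by completed surgery as a labelled sensitivity analysis, with the number of conversions and their complication rate.

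The cost is a short text change. Allocation and conversion are already captured in the eCRF, no further data or patients are needed, and 242 per group still gives a 2.5% error at the margin and 90.1% power at no difference. The only downside is that the reported laparoscopic complication rate may be slightly less favourable.
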